### Plans to promote participant retention and complete follow-up {18b}

Plans to promote participant retention and complete follow-up will include maintaining effective communication with participants to ensure their understanding of the importance of the study and their role. The research study team will provide clear information about the study design, procedures, and potential benefits and risks to participants and will be in personalized contact with participants to help maintaining their engagement and interest in the study, through regular reminders and feedbacks on the progress of the study. Flexibility in scheduling interviews, follow-ups, and accommodating participants’ schedules will help reduce participant burden and increase their willingness to continue participation in the study.

### Data management {19}

All data collected will be hosted by the Swiss TPH. All data will be collected and stored in the form of pseudonyms. In addition, the data will be protected by cryptographic protocols. The secure encryption protocol (SSL protocol) will be used, capable of ensuring the security of communication on the Internet. As soon as the data is transferred to the server and a quality control has been carried out, no data will be stored on the local devices. The SOPs will serve as a guide for all employees on these principles.

### Confidentiality {27}

Data will be stored on a secure and password-protected server at Swiss TPH, Basel. The data will be collected on electronic tablets and will be uploaded on a daily basis in encrypted form. Project data will be handled with discretion and will only be accessible to authorized personnel. On data collection instruments and other project specific documents, participants are only identified by a unique participant number. In order to keep track of individual HCWs during the SW-RCT, each person enrolled will be assigned a code to allow retrieving the same participant at each follow-up step. Codes will only be revealed to the co-PIs in the field and to the research assistants assigned to data collection and destroyed immediately thereafter to protect the respondent and the interviewer. The list linking names and codes will be securely stored at Swiss TPH during the various data collection cycles and will be destroyed once the data has been linked. Only the PI and data analysts will have access to the source documents that link the individuals with the encoded data. Once the data has been encoded, access to the data will be permitted for monitoring, auditing, or data quality assessments.

### Plans for collection, laboratory evaluation, and storage of biological specimens for genetic or molecular analysis in this trial/future use {33}

N/A. The trial does not plan the collection, laboratory evaluation, or storage of biological samples for genetic or molecular analysis.

## Statistical methods

### Statistical methods for primary and secondary outcomes {20a}

Descriptive statistics will be used to summarize the characteristics of HCWs. For the analysis of observed event data, the model applied with the simulated data sets will again be used. HCWs will be considered as separate observational units. For each observation period, the time during which a HCW was under observation will be used as individual offset variable and each HCW will get his/her own random intercept in the analysis. Additional analyses will involve scores reported by the HCW at the end of each period or even during periods. Mixed linear models with robust standard error estimates involving analogous terms as the mixed Poisson regression models will be used; however, without accounting for the time, a HCW has been active during a given period. Analyses addressing the occurrence of severe events will be conducted using mixed logistic regression models. In this case, the outcome is 1 if the respective health worker experienced a severe event in the respective period and 0 otherwise. The structure of these models will be analogous to the one of the models for event rates and scores.

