## Interventions

### Explanation for the choice of comparators {6b}

The comparator will be the current standard of care, which does not include any approach to the management of aggressive or violent behavior by HCWs. The trial will compare within each cluster the incidence of violent episodes and their severity before the introduction of the de-escalation of violence training and the code of conduct with the incidence of violent episodes and their severity from health facilities, after the intervention deployment. The SW-RCT design allows each site to serve as its own control and likely reduces the potential for confounding on cluster and possibly individual-level characteristics.

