### Participant timeline {13}

#### Sample size {14}

Power simulations were performed separately for the study in Iraq and the study in DRC based on the study design scheme given in Table 1. Details of the simulations are provided in an online supplement (see Supplementary file 1). For short, the average number of events per HCWs and 6-month period was assumed to be 1 without intervention, 0.6 after intervention B, and 0.6 in the 6-month period following interventions I and R. A relapse to 0.7 was assumed for the effect of intervention I in the second period after intervention in arms 1, 4, and 7. All effects were assumed to be additive on the log-scale of expected event numbers. We further assumed average event rates to vary between facilities and between HCWs within facilities. Both variations were assumed to follow a normal distribution on the log scale of expected event numbers, with a mean value of 0 and a standard deviation of 0.2. We assumed the probability of a HCW quitting in a given period to be at most 30%. Under these assumptions, 22 health facilities in Iraq with 12 HCW per facility and 33 health facilities in DRC with 5 HCW per facility would provide more than 90% power for finding statistically significant effects of interventions B and I after pooling results from the two countries, assuming a significance level of 5%. The power to detect a significant effect of intervention R after pooling would also exceed 90% if quitting HCWs are replaced one by one.

**Table 1 Tab1:** Participant timeline

			Study periods						
	Allocation		Post-allocation						Close-out
	P1 *0–12 weeks*		P2 *13–37 weeks*		P3 *38–62 weeks*		P4 *63–87 weeks*		*88–99 weeks*
Time points	0	Bas.		FU1		FU2		FU3	
Recruitment									
Eligibility screen	x								
Informed consent	x								
Demographic data	x								
Allocation	x								
Assessments									
Aggression log (continuous)	x		x		x		x		
Health care staff questionnaire		x		x		x		x	
Level of confidence (CCPAI self-efficacy)		x						x	
PTSD Checklist for DSM-5 (PCL-5)		x		x		x		x	
Level of burnout (Maslach burnout inventory scale)		x		x		x		x	
Jefferson physician empathy scale		x						x	
TIS-6 Intention to leave		x		x		x		x	
EQ-5D-5L (EuroQol 5 Dimension 5 Level) Quality of life (QoL)		x		x		x		x	
Assessment of costs		x		x		x		x	
Data analysis and reporting							x		x

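### The stated treatment comparison is before versus after within each facility, and the article names neither a calendar-period term nor a facility effect for the primary model

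*Protocol article*

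**What the plan says.** **Contrast.** Protocol article, Explanation for the choice of comparators {6b}: "The trial will compare within each cluster the incidence of violent episodes and their severity before the introduction of the de-escalation of violence training", set against incidence and severity after deployment. The section says that each site acts as its own control and mentions confounding by cluster and individual characteristics. It does not mention calendar time.

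**Model.** Statistical methods {20a} takes the primary model from the simulations by reference. It adds that "HCWs will be considered as separate observational units", that observation time is an offset, and that "each HCW will get his/her own random intercept in the analysis". No period term and no facility term is named. For the score outcomes, "Mixed linear models with robust standard error estimates involving analogous terms as the mixed Poisson regression models will be used". The logistic models for severe events follow the same structure.

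**Assumed variation.** Sample size {14}: "We further assumed average event rates to vary between facilities and between HCWs within facilities", each with SD 0.2 on the log scale. The simulation details are in Supplementary file 1.

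**Randomised unit.** Sequence generation {16a} randomises health facilities to the steps.

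**The concern.** In a stepped wedge, the share of facilities exposed rises with calendar time. A before/after contrast within a facility therefore carries any trend in the outcome as well as the effect. Trends are plausible here. The outcome is a self-completed log kept for up to 87 weeks in unstable settings, the Iraqi participants are first-year residents gaining experience, and up to 30% of HCWs may leave per period. A fall in true violence, or fatigue in completing the log, would look like benefit; a rise would hide it. The design protects against this only if the analysis compares exposed and unexposed facilities within the same calendar period.

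The second part is precision. HCWs in one facility share the facility's rate. If the model holds only HCW intercepts, it treats colleagues as independent and its standard errors are too small.

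**Working it through.** **1. The plan's own figures.** Table 2 pooled power follows from its country powers by a fixed-effect combination, with the 5% level taken as two-sided:

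pooled power = Φ(√[(z₁ + 1.96)² + (z₂ + 1.96)²] − 1.96), where zᵢ is the normal quantile of country power i.

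- R, 10% quitting (0.73, 0.60): √(2.573² + 2.213²) − 1.96 = 1.434, giving 0.924; stated 0.92.
- R, 20% (0.70, 0.54): 0.898; stated 0.90.
- R, 30% (0.68, 0.54): 0.890; stated 0.89.
- I and B: 0.998 or higher; stated 0.99.

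The pooling reproduces. The country powers cannot be strictly reproduced without Fig. 3 and the supplement.

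**2. Inputs for the conditional checks.** From Sample size {14}: 22 × 12 = 264 HCWs in Iraq and 33 × 5 = 165 in DRC; rates of 1 without intervention and 0.6 after B, and 0.6 after I with relapse to 0.7; facility and HCW SD 0.2 each; quitting 10 to 30%. Assumed: three 11-sequence layouts with 26 post-baseline arm-periods in total, and a rate ratio of 0.6 for R. Method: generalised least squares approximation to a log-link Poisson model, comparing model-based with true (sandwich) standard errors.

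**3. Does Table 2 reveal the model?** Approximate power for I and B:

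| | Iraq | DRC |
|---|---|---|
| No period terms, I and B | 0.99–1.00 | 0.94–0.97 |
| Period and facility terms, I | 0.91–0.95 | 0.77–0.85 |
| Period and facility terms, B | 0.95–0.98 | 0.85–0.91 |
| Table 2, I | 0.97–0.98 | 0.89–0.94 |
| Table 2, B | 0.95–0.97 | 0.87–0.89 |

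For B, Table 2 sits inside the range with period terms. For I, it lies mostly between the two versions. With the layout unknown, this does not show which terms the simulations used.

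**4. Calendar time.** The simplest case needs no layout. If rates fall 10% per period with no intervention effect, a facility with one period before and one after shows a ratio of 0.90. One with one before and three after shows (0.90 + 0.81 + 0.729)/3 = 0.81.

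In the assumed layouts without period terms, and with no true effect (20% quitting, results for I):

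| Fall per period | Spurious rate ratio | False positives, single country |
|---|---|---|
| 10% | 0.88–0.89 | 18–30% |
| 20% | 0.77–0.79 | 52–79% |

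With period terms, the ratio is 1.00 and rejection is 5% in every case.

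These are single-country rates. If both countries shared the trend, the shifts would add. At a 10% fall, rejection rates of 26% (Iraq) and 18% (DRC) in one layout correspond to shifts of 1.315 and 1.039 standard errors. Combined, √(1.315² + 1.039²) = 1.676, or about 39% rejection.

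**5. Facility term.** True error = 2Φ(−1.96 / r), where r is the true standard error divided by the model-based one under an HCW-only intercept.

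- Iraq: r from 1.06 to 1.18, giving about 6.5% to 9.7%.
- DRC: r from 1.02 to 1.07, giving about 5.5% to 6.7%.

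The inflation is moderate because the HCW intercept absorbs much of a constant facility effect. It is larger in Iraq, where there are more HCWs per facility.

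**The case against.** The strongest reply is that this is a condensed article. The primary model is the simulation model, set out in a supplement that was not available, and the simulated data did carry facility-level variation. The sentence on HCW intercepts may only explain how an open cohort with turnover is handled; it does not call that intercept the sole random effect. The before/after sentence is comparator rationale, not an estimator, and sites acting as their own controls is ordinary stepped-wedge language. The 10% and 20% trends are illustrations with no source in the document.

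Much of this stands. A reader might infer that the primary analysis has only an HCW intercept, that secular change will be read as effect, and that the facility is missing from the standard errors. The article does not establish any of these. A reader might likewise infer that robust standard errors are withheld from the Poisson model; the text states them for the linear models and is silent elsewhere. Nor does the plan ignore extra-Poisson variation, since log-normal facility and HCW effects are exactly that.

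What does not fall away is the {6b} sentence. It is the article's only description of the treatment contrast, and it describes the confounded one. The additional-analyses section {20b} does not repair it: an intervention effect that changes over time is effect modification, not adjustment for secular trend.

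**Conclusion.** The point holds as a fault in what is stated, with consequences conditional on the unseen model. The calendar-time part is the main one: followed literally, the stated comparison is biased by any trend, by about the size of a 10% decline per period if that is the trend, and by more if the trend is steeper. The facility part is moderate and depends on the supplement: at most about 10% true error against a nominal 5%.

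The sizes rest on assumed layouts, an assumed effect for R, a two-sided 5% test and illustrative trends. They show what is at stake if the terms are missing, not that they are missing.

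**What to change.** - In {6b}, replace the before/after sentence with a comparison of exposed and unexposed facility-time adjusted for calendar period.
- In {20a}, state that the mixed Poisson model, and the analogous linear and logistic models, include fixed period effects by country and a facility random intercept with HCWs nested within facility.
- Facility-by-period effects, a negative binomial model and small-sample corrections are optional sensitivity analyses, not requirements.

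**Cost.** If the supplement already has these terms, the change is wording only. If not, confidence intervals widen slightly and country-level power may fall below Table 2, most visibly for I in DRC (0.77–0.85 against 0.89–0.94). The claim that the sample "would provide more than 90% power for finding statistically significant effects of interventions B and I after pooling results from the two countries" should survive. Combining the lowest approximate values by the formula above gives 0.99 for I (0.91 with 0.77) and above 0.99 for B (0.95 with 0.85).

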## Data collection and management

### Plans for assessment and collection of outcomes {18a}

In all arms, incidence and severity of episodes of violence will be collected by each consenting HCW (self-reported) via the *Aggression log*, longitudinally, during the initial observation period (P1) of 12 weeks and during the whole duration of the trial. This instrument will capture the frequency and description of the incident experienced during the working hours and will allow the staff to judge the severity of the incident via a 100-mm visual analogue scale (VAS). The *Aggression log*, adapted from Morken et al., was customized based on qualitative insights, and simplified for user-friendliness, incorporating feedback from healthcare personnel and experts in both countries, ensuring efficient reporting despite demanding work pressure [50]. The tool will be completed by the HCWs and each time the HCWs are exposed to aggressive behaviors, defined as any verbal, non-verbal, or physical behavior that was threatening or physical behavior that was adding arm. Entries will include time of incident, perpetrator’s gender, type of assault, whether verbal (e.g. verbal threat, insult) or physical, means used by the aggressor and consequences for the victim. Participants will be assured confidentiality and anonymity of their responses through unique identifiers, and a secure reporting system will be established.

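### If the per-incident severity VAS enters the planned linear score models, its effect estimate rests only on incidents that occurred and could be biased in either direction

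*Protocol article*

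**What the plan says.** All references are to the protocol article.

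- **Statistical methods {20a}.** After the Poisson model for event counts, the article adds: "Additional analyses will involve scores reported by the HCW at the end of each period or even during periods". For these scores, "Mixed linear models with robust standard error estimates involving analogous terms as the mixed Poisson regression models will be used". The same section plans a mixed logistic model for severe events, in which "the outcome is 1 if the respective health worker experienced a severe event in the respective period and 0 otherwise".
- **Plans for assessment {18a}.** The Aggression log "will allow the staff to judge the severity of the incident via a 100-mm visual analogue scale (VAS". It is filled in "each time the HCWs are exposed to aggressive behaviors", so a period without an incident produces no VAS value.
- **Table 1 (Participant timeline).** The Aggression log is the only instrument marked as continuous. All other scales sit at baseline and the follow-up visits.
- **Choice of comparators {6b}.** The intended contrast covers "the incidence of violent episodes and their severity before the introduction" of the interventions, set against the same quantities afterwards. The Objectives section also names severity beside incidence.

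**The concern.** The only score in this document that can be reported during a period is the VAS, and it is attached to incidents. A linear model of VAS, whether by incident or as a mean per HCW-period, uses only those HCW-periods in which something was logged.

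The number of incidents is the primary endpoint and the thing the interventions should reduce. Control and intervention periods would therefore be compared on different selections of incidents. Randomising the crossover order does not protect a comparison made within a subset that treatment itself determines.

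The mix can change in two ways: the interventions may prevent some kinds of incident more than others, or trained and unblinded HCWs may log mild events more readily. Either can move mean VAS although no given kind of incident has become more or less severe. The methods in section {20c} do not repair this. Imputation and weighting address values that exist but were not recorded, whereas the severity of an incident that did not happen is undefined.

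**Working it through.** **The plan's own figures.** The article gives no figure for the severity-score analysis. Its pooled power in Table 2 concerns event counts. It is reproduced by inverse-variance pooling of the two countries, Φ(√[(z_Iraq + 1.96)² + (z_DRC + 1.96)²] − 1.96). For the refreshment intervention at 10% quitting, country powers of 0.73 and 0.60 give 0.924 (stated 0.92). All nine pooled entries agree within 2 points. The country-level powers cannot be rebuilt without the design figure and the supplement.

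**Inputs from Sample size {14}.** Events per HCW per six months: 1 without intervention, 0.6 after one intervention. Effects add on the log scale, so training plus board gives 0.6 × 0.6 = 0.36. Facility and HCW log-scale SDs are 0.2 each, so the variance is 0.04 + 0.04 = 0.08. There are 22 × 12 + 33 × 5 = 264 + 165 = 429 HCWs.

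**Step 1: who has a severity score?** P(no incident) = E[exp(−λeᵘ)], with u normal, mean 0, variance 0.08.

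- λ = 1: 0.368, so 63% have at least one VAS value.
- λ = 0.6: 0.544, so 46%.
- λ = 0.36: 0.691, so 31%.

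Without the random effects, exp(−1) = 0.368, exp(−0.6) = 0.549 and exp(−0.36) = 0.698, so the result hardly depends on them.

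**Step 2: what happens to mean VAS?** The document gives no severity distribution. Assume 70% mild incidents at 20 mm and 30% severe at 70 mm. Mean VAS = (20 × mild + 70 × severe) / (mild + severe).

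| Scenario | Mild rate | Severe rate | Mean VAS | Shift | Summed VAS | P(severe event) |
|---|---|---|---|---|---|---|
| No intervention, rate 1 | 0.70 | 0.30 | 35.0 | – | 35.0 | 0.27 |
| Rate 0.6, only mild prevented | 0.30 | 0.30 | 45.0 | +10.0 | 27.0 | 0.27 |
| Rate 0.6, proportional | 0.42 | 0.18 | 35.0 | 0 | 21.0 | 0.17 |
| Rate 0.6, severe first | 0.60 | 0 | 20.0 | −15.0 | 12.0 | 0 |
| Rate 0.36, only mild prevented | 0.06 | 0.30 | 61.7 | +26.7 | 22.2 | 0.27 |

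The last column includes the random effects and covers all HCW-periods, with no incident counted as 0.

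Mean VAS can also rise when both kinds of incident fall. If mild incidents fall by 50% and severe by 25%, it is (0.35 × 20 + 0.225 × 70) / 0.575 = 22.75 / 0.575 = 39.6, against 35 before. If only mild incidents fall by 50%, it is (0.35 × 20 + 0.30 × 70) / 0.65 = 43.1.

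For changed logging, write m for the mild share of logged incidents. Mean VAS is 20m + 70(1 − m) = 70 − 50m, so each 10-point rise in m lowers the mean by 5 mm with no real benefit.

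**Step 3: range.** Mild shares of 60–90% and VAS pairs of 20/70 or 30/60 were tried. At rate 0.6, preventing only mild incidents raises mean VAS by 2.0 to 13.3 mm, and preventing severe ones first lowers it by 3 to 20 mm. At rate 0.36 the mild-only rise is 5.3 to 26.7 mm. That range covers mild shares of 70–90%, because at 60% there are too few mild incidents to prevent.

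**Step 4: simulation.** A simplified before/after layout of 429 HCWs used the 70/30 mix, VAS SD 10 within each kind, and only mild incidents prevented to rate 0.6. A linear model of incident VAS with an HCW random intercept gave +9.8 mm on average, positive with p < 0.05 in 40 of 40 replicates. The risk of a severe event changed by −0.006. The layout was not the stepped wedge, and p-values were model-based rather than robust.

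**The case against.** **The VAS is not named in {20a}.** The text could mean only the psychosocial scales, which are taken whether or not an incident occurred. This stands in part: use of the VAS is an inference, so the point is conditional. The alternative is weak, however. The baseline questionnaire falls in the last two weeks of the first period, which makes it an end-of-period measurement, and nothing but the log is collected continuously.

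**HCWs are the observational units, which suggests one score per HCW-period, not one row per incident.** This is fair, but a mean per HCW-period is equally undefined without an incident. A sum with zeros would avoid the problem. The article does not state one, and that detail could sit in an analysis plan not shown here.

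**The severe-event logistic model already handles severity.** This stands and sets the limit of the point. A reader might infer that the trial's whole severity conclusion could come out in the wrong direction. The document does not support that: the logistic model codes no-incident periods as 0, and in the scenarios above it shows a reduction or no change, never a worsening.

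**The direction rests on assumed inputs.** This also stands. A reader might infer that the linear model must show worse severity. It need not: proportional prevention gives no shift, and training meant to defuse situations early could plausibly remove severe incidents first.

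**VAS severity is not a listed phase 2 endpoint.** True; any such model is one of the additional analyses.

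**Conclusion.** The point holds in conditional form. If the Aggression log VAS is what {20a} means by scores reported during periods, as Table 1 and {18a} strongly suggest, the linear model conditions on a post-randomisation outcome that the interventions are designed to change. On the article's own rates, the HCW-periods contributing a score fall from about 63% to 46% or 31%. The resulting shift in mean VAS ranges from −20 to +13.3 mm at rate 0.6 across the assumed mixes. It is upward if mainly mild incidents are prevented, downward if severe ones go first or more mild events are logged, and zero if prevention is proportional.

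The shares, VAS values and prevention patterns are assumptions; the document gives none. The problem is confined to the VAS-score analysis. The primary count model, the end-of-period scales and the severe-event model do not share it. It still deserves correction, because two severity analyses in one plan could disagree and no order of precedence is stated.

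**What to change.** In {20a}:

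1. Limit the linear score models to scales measured on every HCW regardless of incidents.
2. Name the severe-event logistic model as the main severity analysis.
3. If VAS is also analysed for effect, use a measure defined for every HCW-period, such as summed VAS with 0 for no incident, with the primary model's terms, a log-time offset, and robust or overdispersion-adjusted standard errors. The offset matters because the first period lasts 12 weeks and later ones 25 (for example, weeks 13 to 37).
4. Report mean VAS per incident as descriptive only, with no effect claim.

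The cost is wording; all the data are already logged. The drawback is that summed VAS mixes frequency with severity. In the 50%/25% example it falls by 35% (35 to 22.75) while the count falls by 42.5% (1 to 0.575), so it cannot show that incidents became milder. Nor does it remove changes in reporting. Both limits should be stated when it is interpreted.
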